## 2.6 Exclusion criteria:

Mothers:

1. Who have had breast surgery
2. Who do not understand French or English
3. Who are unable to present to the clinic (transport not available)
4. Who have birthed multiples or preterm
5. Whose infants are exclusively formula-fed
6. Who are adoptive mothers
7. Who have been identified with a psychological risk that may impede her ability to attend the first appointment at the clinic

## 3 Methods:

### 3.1 Participant recruitment and informed consent

Upon arrival flyers (see section 8.9) will be handed out by a healthcare professional to eligible mothers. Mothers who have read the flyer and are interested in discussing the study will inform their healthcare provider or contact the research coordinator to speak with the study staff. If a woman declines to meet with the study staff, there will be no further contact.

Women who agree to meet with the research staff but are then found to be ineligible or decline to participate will not be enrolled in the study and will not be contacted further. However, the research staff will record the date of the meeting with the participant and the reason for not participating in the study.

A consent form will be given to the participant in either French or English. Participants will be asked for their contact information what time of day is best to contact them.

### 3.2 Events prior to hospital discharge

#### 3.2.1 Data collection

Once consent has been obtained, the research team will collect information about delivery (mode of delivery and date and time of birth), obstetrical (previous pregnancies, parity) history, and information on the baby (gender, ethnicity, gestational age at birth, birth weight, Apgar score, bilirubin levels (TCB [trans cutaneous bilirubin] and/or TSB [total serum bilirubin], whether supplementation was given and date and time of discharge) from the hospital chart.

Contact information will be recorded in the study master log. As well, the OHIP number will be recorded in the master log to eventually allow the linkage of the dataset to ICES administrative data.

Upon confirmation by the pediatrician, the obstetrician, the family physician, and/or the midwife in attendance that the mother and baby have no counter-indication for early discharge, the research team will proceed to randomize the participant.

#### 3.2.2 Randomization

Study participants will be randomly assigned to either the intervention (discharge with follow-up at the breastfeeding clinic) or the control (standard of care) groups via a 2:1 allocation ratio, with group designations being determined after the patient is enrolled and informed consent is obtained. Stratification will be used to improve allocation balance by site of recruitment and parity of participants. Group designation is given from a randomization list, which will be generated using a permuted randomized block design, with permuted blocks of sizes 3, 6, and 9 units, prior to study initiation. This list is then entered directly into REDCap's group allocation component which assigns group placement based on the inputted randomization list at the time of initial data entry, all the while blinding the study researchers, recruiters, and participants to the randomization allocations prior to patient enrollment and data collection. The study staff will then inform the participant of their randomization group. Rather than occurring at the time of consent, randomization will be delayed until confirmation by the nurses and/or attending physicians that the participant is indeed a candidate for discharge at approximately 24h ( $\pm$  12) after vaginal or 48h ( $\pm$  12) after C section delivery.

[figure not shown]

**FIGURE 1. Schematic diagram showing the two possible outcomes after randomization.** In the case of this breastfeeding study, the participants may be assigned the standard-care or the post-partum clinic option.

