## **2 Aim of Study and Study Design**

### **2.1 Study Objectives**

We will enroll women meeting the inclusion and exclusion criteria for the trial. The objectives of this study are to:

1. Determine if care provided through this community based postpartum clinic can improve duration and rate of exclusive breastfeeding, prevent costly postnatal problems and reduce length of hospital stay and the number of readmissions for new mothers.
2. Determine the level of satisfaction of the mothers attending this clinic with the care they received.
3. Determine the cost effectiveness of the new clinic and what the costs are associated with implementing a community-based postpartum clinic.
4. Determine the feasibility of operating this type of clinic in other settings across Ontario.

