## 2.4 Secondary Outcomes

1. Rates of hyperbilirubinemia requiring phototherapy or hospitalization
2. Poor infant weight gain requiring intervention (pumping, supplementation, hospitalization)
3. Incidence of breastfeeding difficulties (e.g., sore nipples, insufficient milk supply, inadequate latch, engorgement)
4. Breastfeeding self efficacy score (Breastfeeding Self Efficacy Scale or BSES) at 2 weeks, 1 month and 3 months
5. Score of the Edinburgh Post-partum Depression Scale for new mothers
6. Access to community-based services: Public Health Clinics, Family Doctor, Pediatrician
7. Number of emergency department visits for the mother and the baby
8. Number of hospital readmissions for the mother and her baby
9. Mothers' satisfaction with the support received
10. Length of stay in the hospital, from delivery to discharge
11. Costs associated with this community-based postpartum clinic.

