## 2.5 Inclusion criteria:

Mothers having delivered a baby at The Ottawa Hospital - General or Civic Campus:

1. Who are  $\geq 18$  years at the time of enrollment
2. Who are any parity, with a singleton infant born  $> 36 + 6$  weeks of Gestational Age
3. Who have no medical counter indication for discharge at 24 ( $\pm 12$ ) hours post vaginal delivery or 48 ( $\pm 12$ ) hours post C-section delivery and for which the physician (family physician or obstetrician) has agreed that the mother is eligible
4. Who are breastfeeding and intend to breastfeed their baby upon discharge
5. Whose infant is healthy with no counter indication for discharge at 24 ( $\pm 12$ ) hours post vaginal birth or 48 ( $\pm 12$ ) hours post C-section birth and for which the physician (family physician or paediatrician) has agreed that the infant is eligible
6. Who can be contacted by phone or E-mail after hospital discharge

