### **3.3 Non-intervention arm post-discharge events**

Women randomly assigned to the non-intervention arm option will be discharged according to the current hospital standards, in accordance with their physician or midwife's decision. After hospital discharge, the participant and her baby will be entitled to receive follow-up care and seek breastfeeding support that is currently available in the community (e.g. through their family doctor, Public Health Unit or private services), but may not attend the pilot breastfeeding clinic.

Women will be contacted at 2 weeks, 1 month and 3 months post-delivery to complete the different surveys and questionnaires (3.5).

As is current standard of care practice, women will be assessed by Public Health Nurses for post-partum depression shortly after birth. Services will be provided as per the standard.

As part of the research, women will be contacted by phone at 3 weeks by a Public Health Nurse to administer the Edinburgh Postnatal Depression Scale. In the event of a high score, the Ottawa Public Health Nurse will provide the participant with appropriate support. Information collected will be abstracted by the research staff.

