### **3.4 Intervention arm post-discharge events**

Women randomly assigned to the intervention will be discharged approximately 24 hours following a vaginal delivery or approximately 48 hours following a C-section. While this is the aimed ideal time of discharge, there may be variation as time of discharge will ultimately depend on the attending physician/midwife's opinion/orders and what he/she feels is in the best interest of the mother and her newborn. Women who choose to stay in the hospital longer will still be referred to the Monarch Clinic and will not be excluded from the study.

Women and their infants will be expected to attend a pre-booked appointment at the breastfeeding clinic, scheduled within 48 hours of their discharge. Clinic staff will follow up with the participant if she fails to keep the mandatory follow-up appointment. This first appointment will include maternal assessment and care (e.g., wound care, prescriptions), neonatal care (e.g., tongue-tie clips, jaundice screening using transcutaneous bilirubinometer), blood work including TSB (samples couriered to TOH central laboratory, HBHC postpartum assessment, and breastfeeding assessment and support. Family physicians will be available for on-site consultations in the mornings, and lactation consultants and registered nurses will be at the clinic throughout the day from Monday to Friday and Saturday mornings. Medical data (e.g., bilirubin level (transcutaneous and serum), newborn assessment, infant weight gain, urination and defecation frequency, breastfeeding assessment and progress, maternal care) found in the clinic chart will be gathered.

The Bilirubin Pathway, established by the CMNRP, will be used to guide for the management of neonatal jaundice. Those guidelines provide recommendation for subsequent TSB and or TCB follow-up, according to the modified Buthani's normogram and whether risk factors for hyperbilirubinemia are

present or not. For babies discharged before 24 hours, blood for the newborn screening will be drawn at the first visit and sent by mail to the Newborn Screening Ontario laboratory located at CHEO.

Additional follow-up visits at the breastfeeding clinic will be made available to participants for the month following the birth of their baby.

Participants in the intervention group will also be contacted at 2 weeks, 1 month and 3 months to complete the different surveys and questionnaires (3.5).

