### 4.3 Statistical analysis

All outcomes will be analyzed based on the intention-to-treat principle, in accordance with the randomization allocations described previously. The primary goal of this study is to test the hypothesis that rates of exclusive breastfeeding at 3 months (defined as the feeding of only the infant's mother's milk for at least 2 weeks prior to collected outcome) will be higher in the group of women attending the post-partum clinic, as compared to those under standard of care. For comparison between intervention and control arms we will employ a generalized estimating equation multivariable regression model to account for prognostic risk factors that have not been sufficiently balanced by randomization. Group and individual level covariates will be included in the model, with recruitment site as the clustering unit to allow for inference at the individual level. This design will also investigate the effect of demographic

drivers such as maternal age, education, parity, etc., on the primary outcome, producing both crude and adjusted risk estimates and their 95% confidence intervals.

Secondary outcomes will be collected by studying the medical data (such as rates of hyperbilirubinemia and self-efficacy) that will be entered in the database by the research staff. This data will be compared across case and control groups using the Pearson Chi-squared, Student's t, or Fisher's exact test, depending on their observed frequencies. We will also compare the statistics and outcomes from the present study with baseline estimates from phase 1. The answers women provide through their questionnaires and surveys will be the main instruments for determining exclusive breastfeeding rates and their behavioral and emotional measurements. For the cost-effectiveness analysis, direct and indirect costs for the intervention and control groups will be compared regarding use of resources (e.g., clinic visits, physician visits, Emergency Department visits, hospital readmission, and indirect cost).

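### Length of stay falls under a crude two-group test although intended discharge timing differs by 24 h between delivery modes; adjusting for mode would make it more precise at no cost

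*Protocol*

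**What the plan says.** - **Eligibility (2.5, criteria 3 and 5).** Mother and infant must be fit for discharge at "24 ( $\pm 12$ ) hours post vaginal delivery or 48 ( $\pm 12$ ) hours post C-section delivery". The infant criterion uses the same windows.
- **Intended discharge, intervention arm (3.4).** Women are to be "discharged approximately 24 hours following a vaginal delivery or approximately 48 hours following a C-section". The section allows a longer stay on the clinician's decision or the woman's choice.
- **Discharge, control arm (3.3).** Women "will be discharged according to the current hospital standards". No hours are given.
- **Randomisation (3.2.2).** "Stratification will be used to improve allocation balance by site of recruitment and parity of participants". Delivery mode is not named.
- **Outcome (2.4, item 10).** "Length of stay in the hospital, from delivery to discharge", with no split by mode. Objective 1 (2.1) includes the aim to "reduce length of hospital stay and the number of readmissions for new mothers".
- **Analysis (4.3).** Secondary data are to be "compared across case and control groups using the Pearson Chi-squared, Student's t, or Fisher's exact test". The multivariable GEE model in the same section is set out under the primary outcome. The covariates it gives as examples are maternal age, education and parity.
- **Data (3.2.1).** Mode of delivery, time of birth and time of discharge are all taken from the hospital chart.

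**The concern.** The protocol ties the timing of discharge to delivery mode. The eligibility windows run from 12 to 36 h after vaginal birth and from 36 to 60 h after C-section, and they meet only at 36 h. If actual stays follow this pattern even roughly, mode will be a strong predictor of length of stay. A crude t-test ignores it, so the spread between modes is counted as residual noise and widens the confidence interval for the arm difference.

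What is at stake is precision for an outcome named in Objective 1. The variable that would recover the precision is already collected. It is also known before allocation, because randomisation waits for a discharge check that is itself specific to the mode of delivery (3.2.2).

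**Working it through.** The protocol gives no SD, target difference or power for length of stay, so there is no figure of its own to reproduce. The check shows how much precision the crude test gives up under stated assumptions.

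**Inputs from the protocol**
- Window centres of 24 h and 48 h (2.5, 3.4), a gap of 48 − 24 = 24 h.
- Arm sizes of 306 intervention and 154 control (4.1).

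**Assumptions not in the protocol**
- C-section share q = 0.30.
- A realised gap in mean stay of 24 h in both arms.
- Within-mode SD s of 7, 12 or 18 h, the same in both modes and both arms.
- Stay recorded for all 460 women.

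**Step 1. Variance due to mode.** q(1 − q) × 24² = 0.21 × 576 = 121 h².

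**Step 2. Standard error factor.** √(1/306 + 1/154) = 0.0988.

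**Step 3. Crude and adjusted standard errors.** Crude SE = √(s² + 121) × 0.0988. Adjusted SE = s × 0.0988. Share of variance due to mode = 121/(121 + s²).

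| Within-mode SD | Share due to mode | Crude SE | Adjusted SE |
|---|---|---|---|
| 7 h | 71% | 1.29 h | 0.69 h |
| 12 h | 46% | 1.61 h | 1.19 h |
| 18 h | 27% | 2.08 h | 1.78 h |

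At SD 12 h the 95% half-width goes from 1.96 × 1.61 = 3.15 h to 1.96 × 1.19 = 2.32 h (unrounded SEs used).

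**Step 4. Wider range.** With q from 15% to 40% and s from 6 to 18 h, the crude variance is 1.23 times the adjusted variance at the low end (q = 15%, s = 18 h) and 4.84 times at the high end (q = 40%, s = 6 h).

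**Step 5. Is chance imbalance in C-section share a separate problem?** The SD of the difference in share between arms is √0.21 × 0.0988 = 0.045, or 4.5 percentage points. Multiplied by 24 h, this shifts the crude difference by 1.09 h (1 SD). Combining it with the adjusted SE at s = 12 h gives √(1.19² + 1.09²) = 1.61 h, which is the crude SE. The imbalance is therefore the very component that makes the crude SE larger, and the crude confidence interval already covers it.

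**The case against.** The strongest reply is that nothing here is an error. An unadjusted comparison of randomised arms is unbiased over randomisation, and its standard error allows for chance differences in case mix. Site and parity are a legitimate choice of stratification factors. This stands, and it makes the point one of efficiency.

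Four stronger readings might tempt a reader, and the documents do not support them.

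- **That leaving mode out of the stratification biases the comparison.** It does not. A 2-SD imbalance in C-section share would move the crude estimate by about 2 × 1.09 = 2.2 h under the assumptions above, but this is random error already inside the crude interval. It is neither a bias nor a second problem.
- **That mode shifts actual stays by 24 h by design.** Section 2.5 sets fitness for discharge and does not report observed stays. Controls follow unspecified hospital standards (3.3), and women in the intervention arm may stay longer (3.4). The realised gap is an assumption.
- **That the imprecision carries into the cost comparison.** The resources listed as examples in 4.3 do not include the initial stay, so the link is not stated.
- **That the randomisation scheme is deficient.** Adjustment in the analysis recovers the precision without changing it.

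A further reply is that covariates for one of eleven secondary outcomes belong in a statistical analysis plan, which may exist and is not shown. This stands only in part. The secondary-outcome text in 4.3 is generic and does not name length of stay, but it does name the tests, and every one is a crude two-group test. The GEE sentence shows that adjustment was considered. Its most natural reading is the primary outcome, and delivery mode appears nowhere in 4.3.

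**Conclusion.** The point holds as a no-cost improvement to a secondary outcome. As written, 4.3 gives length of stay a valid but needlessly imprecise test. The direction of the loss needs only that both modes are represented and that their mean stays differ. Its size depends on the C-section share, the realised gap and the within-mode spread, none of which the protocol gives. At 30% C-section and a 24 h gap in both arms, the SE reduction ranges from large (1.29 to 0.69 h at SD 7 h) to modest (2.08 to 1.78 h at SD 18 h). A smaller realised gap would shrink the gain. Since the protocol sets no target difference or power for this outcome, no stated design goal is shown to fail. The primary analysis is not affected.

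**What to change.** In section 4.3, add that length of stay will be compared between arms with a linear model containing arm, mode of delivery, site and parity, with heteroscedasticity-robust standard errors, and will also be summarised by delivery mode. If a statistical analysis plan already specifies such a model, bring 4.3 into line with it.

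The robust standard errors allow for spread that differs by mode or arm. Changing from Student's t to a Welch test would not be enough, because it would still leave the variation between modes in the error term.

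The cost is one sentence. Mode, times of birth and discharge, site and parity are already to hand, mode is fixed before allocation, and the randomisation list and the clinical procedures need no change.

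### The protocol prints every block size in an open trial whose own team randomises and learns each arm, so upcoming allocations are modestly predictable

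*Protocol*

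**What the plan says.** Protocol section 3.2.2 assigns women "via a 2:1 allocation ratio" in favour of the clinic. On strata it says: "Stratification will be used to improve allocation balance by site of recruitment and parity of participants". The list is generated before the study starts from "permuted blocks of sizes 3, 6, and 9 units" and loaded into REDCap. The section describes this as "blinding the study researchers, recruiters, and participants to the randomization allocations prior to patient enrollment and data collection". Nothing in the protocol reserves the block sizes for the person who makes the list.

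Allocation is open once made: "The study staff will then inform the participant of their randomization group". Section 3.2.3 adds that clinic women have an appointment booked before discharge.

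On who acts and when, section 3.2.1 says that after clinicians confirm there is no reason against early discharge, "the research team will proceed to randomize the participant". Section 3.2.2 agrees that "randomization will be delayed until confirmation by the nurses and/or attending physicians".

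**The concern.** Concealment needs two things: nobody can read the list, and nobody can work out the next entry from earlier ones. REDCap secures the first. Printing the ratio, the strata and all block sizes in the protocol weakens the second, because the team that randomises also learns every arm.

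What is at stake is selection bias. Exclusive breastfeeding at 3 months is taken from mothers' questionnaire answers (section 4.3) and plausibly depends on motivation. If a foreseen arm influenced which cleared woman was randomised next, or whether a doubtful case went forward, the arms could differ in motivation from the start.

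The schedule has no measure that would show this. Self-efficacy is first measured at 2 weeks and socio-demographics at 1 month (section 3.5). The data collected before discharge (section 3.2.1) cover delivery, obstetric history and the baby.

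**Working it through.** The protocol gives no figure for predictability, so there is none to reproduce.

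**Inputs**
- Block sizes 3, 6 and 9, and ratio 2:1 (section 3.2.2). A block of size b holds 2b/3 clinic and b/3 control places.
- Two campuses (section 2.5: "Mothers having delivered a baby at The Ottawa Hospital - General or Civic Campus") and stratification by parity. The number of parity levels is not stated. Assuming two levels and equal strata, 460 / (2 × 2) = 115 women per stratum.
- How often each size is used is not stated. Equal use is assumed, and other weights were tried.

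**Formula.** The observer knows the set of sizes and all earlier arms in the stratum, but not the size of the current block. Let w be the current probability of being in a block of size b with c control and t clinic places already used. Then

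P(next is clinic) = Σ w × (2b/3 − t) / (b − c − t),

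with w updated by Bayes' rule after each allocation.

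**Worked steps at the start of a stratum**
- First woman is control. This has probability 1/3 under each size, so the weights stay equal. P(next clinic) = (2/2 + 4/5 + 6/8) / 3 = (1 + 0.80 + 0.75) / 3 = 0.85.
- First two women are clinic. The likelihoods are 2/3 × 1/2 = 0.333, 2/3 × 3/5 = 0.400 and 2/3 × 5/8 = 0.417, which sum to 1.150. P(next clinic) = (0.333 × 0 + 0.400 × 2/4 + 0.417 × 4/7) / 1.150 = 0.438 / 1.150 = 0.38. Control is therefore 62% likely. With fixed blocks of 3 it would be certain.

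**Check of the method.** For fixed blocks of 3, the expected correct guesses per block are 2/3 + (1/3 × 1 + 2/3 × 1/2) + 1 = 7/3, or 77.8% per allocation. Simulation gave 77.6%.

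**Results by simulation, 115 women per stratum, equal weights.** Always guessing clinic is right 66.7% of the time. Small differences between runs are simulation error.

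| Sizes | Correct guesses | Certain allocations | P(clinic) at least 0.9 |
|---|---|---|---|
| 3, 6, 9 | 73.7–73.8% | 3.8–3.9% | 13.0–13.2% |
| 6, 9 | 73.0–73.2% | 5.1–5.5% | 14.3% |
| 6, 9, 12 | 71.7–71.9% | 2.1–2.2% | 7.8% |

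For 3, 6, 9 the certain allocations split into 3.1% clinic and 0.8% control. Control is at least as likely as clinic for 18.0% of allocations, and about 70% of those turn out to be control.

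**Sensitivity for 3, 6, 9.** Unequal weights (0.6/0.3/0.1, 0.8/0.1/0.1 and 0.1/0.3/0.6) give 73.0% to 75.8% correct and 1.5% to 5.4% certain. Across equal and unequal weights, 12% to 37% can be called for either arm with more than 90% confidence. Strata of 20, 60 or 230 women give 72.8%, 73.6% and 73.7% correct.

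**Scale of a possible bias.** Suppose women randomised when clinic looks likelier than 2/3 have a success rate d points higher than average, and those randomised when it looks less likely have one d points lower. The arm difference is then biased by about 0.77d (0.72d to 0.89d across weights). The protocol gives no value for d. If d is 1 point the bias is 0.8 points, and if d is 5 points it is 0.77 × 5 = 3.9 points. This is a ceiling, since it needs action on every prediction.

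**The case against.** **The list is concealed.** This is correct. The blinding statement concerns the list in REDCap, and printing the sizes does not contradict it. The weakness is prediction from history.

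**The team does not choose when to randomise.** A reader might infer that it does, because it performs the step. The text does not support that: clinicians' confirmation is the trigger, the women have already consented, and the discharge window is short. What remains is some discretion after clearance, for example over order on a day with several cleared women. That is inferred, not stated.

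**Perfect tracking is unrealistic.** The figures need a faultless tally for each site-by-parity stratum. With four interleaved strata, someone who recalls only the last four allocations trial-wide sees P(clinic) stay between about 0.61 and 0.76. Nothing says that staff study the block sizes or keep tallies. This stands, and it makes the figures upper bounds.

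**Confident foresight is mostly of clinic.** This also stands. Clinic is already expected two times in three, and control, the arm staff might wish to avoid, is certain in only 0.8% of allocations.

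**The block of 3 looks like the culprit.** It is the smallest block possible at 2:1, so the reading is tempting, but the figures do not bear it out. Using 6 and 9 alone leaves correct guesses almost unchanged and raises certain allocations from about 4% to over 5%.

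**Adjustment would deal with it.** In part. Section 4.3 adjusts for prognostic factors and names maternal age, education and parity. Selection through those would be reduced, but selection on unmeasured motivation would not.

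**Conclusion.** The point holds as a minor weakness in the design. Knowing the printed sizes lifts the best achievable guess by about 7 percentage points, from 67% to 74%, with about 4% of allocations certain and control certain in under 1%. These are upper bounds for a perfect per-stratum tally, equal block-size weights and about 115 women per stratum (two parity levels assumed). Bias in the primary comparison is possible through unmeasured motivation, but its size cannot be fixed from the protocol. The documents do not show that concealment has failed or that anyone would act on a prediction. The case for change is that the disclosure serves no purpose in the protocol and is almost free to remove.

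**What to change.** In section 3.2.2, delete the block sizes and say instead that block sizes vary at random and are held in a restricted document by the list's author. Because 3, 6 and 9 are already disclosed, generate the list before the trial starts from a different, undisclosed set of varied sizes.

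Non-disclosure is the main remedy, and larger sizes alone do less. Even for an observer who knew them, 6, 9 and 12 would lower correct guesses only to about 72%. That set would also raise the share of allocations where control is at least as likely as clinic from 18.0% to 20.5%, though those calls would be less accurate (about 63% control against 70%). Removing only the block of 3 should not be presented as a solution.

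The cost is one sentence and one generated list. If the new blocks are larger, imbalance within a site-by-parity stratum may be slightly greater, which matters little at about 115 women per stratum.
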